#### Study duration

The Aftercare intervention commenced receiving referrals on 21 August 2017 from the emergency department of the largest hospital in the region, the Wollongong Hospital, and following the receipt of human research ethics approval, recruitment of study participants commenced on 1 November 2017. The service was rolled out gradually, so the full implementation of the intervention, including referrals from all three participating emergency departments, occurred on 5 March 2018. Data will continue to be collected for 12 months following the recruitment of the 75th intervention group study participant. As such, data collection for the study is forecast to cease by November 2020.

### Study sample

Participants in the Aftercare intervention will be drawn from people who attend one of the three participating emergency departments as a result of a suicide attempt or high risk for suicide, who meet the referral inclusion criteria. Participants’ risk for suicide (and therefore suitability for the Aftercare intervention) will be determined by the hospital staff using standard mental health assessment protocols. Those considered for referral to the Aftercare intervention will be 16 years of age and over. Those excluded from consideration for the service will be admitted to the hospital as an inpatient, or being actively case managed by mental health services, at that time of presentation to the emergency department. Those who consent to participate in the Aftercare intervention and who consent for their data to be included in the study will form the intervention group for the study.

The control group (TAU) will be sourced via de-identified hospital data extraction. They will be people 16 years of age and over who attend a participating emergency department as a result of a suicide attempt or high risk for suicide but either do not receive, or do not accept, a referral to the Aftercare intervention (i.e. did not wish to participate in the service; were unable to participate for other reasons e.g., time commitments; or had not received a referral to the service e.g. standard procedures were not followed in the emergency department). Pre-determined hospital codes for suicide attempt or high risk for suicide will identify controls. They will be selected by identifying those patients who presented to any of the emergency departments in the study during the study period, and identifying those who presented in the same month, who met the study inclusion criteria, and who had the closest emergency department presentation dates to the participants undertaking the Aftercare intervention and enrolled in the trial*.* A human research ethics waiver for consent was granted; all data is sourced via hospital data and code sets.

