#### Inclusion and exclusion criteria

Health consumers who are aged 16 years of age and over who present to an emergency department with significant suicidality will be considered for the Aftercare intervention. They will be ineligible to participate if they are admitted to the hospital as an inpatient, if they are being actively case managed by the local health district’s mental health services, or if they have cognitive impairment sufficient to preclude full participation in, or comprehension of, the intervention as assessed by the referring clinician.

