### Sample size and statistical power

The sample size required to achieve power of 80% was estimated for the primary analyses using G*Power [87]. Local hospital data (2014/2015 year) indicated that approximately 1340 people present to emergency departments with suicide-related presentations annually and systematic reviews have estimated that 16% re-attempt suicide within 12 months [5]. Based on Hvid et al.’s [30] report that an intervention group had approximately half the rate of deaths by suicide than a TAU group at 12 months (.087 vs .219), the sample size required for a log-rank test at α level .05 is 75 participants in the intervention group and 1265 participants in the control group.

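### No sentence applies the exclusions for admission, active case management and cognitive impairment to controls, so as written ineligible people can enter the control arm only

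*Protocol article*

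**What the plan says.** **Controls** (protocol article, Study sample). They are people aged 16 or over who attend a participating emergency department for a suicide attempt or high risk, "but either do not receive, or do not accept, a referral to the Aftercare intervention". The reasons offered are declining, being unable to take part, or that the person "had not received a referral to the service e.g. standard procedures were not followed in the emergency department". On identification the text says: "Pre-determined hospital codes for suicide attempt or high risk for suicide will identify controls". Selection then proceeds by "identifying those who presented in the same month, who met the study inclusion criteria, and who had the closest emergency department presentation dates", with enrolled participants as the reference.

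**Participants** (Study sample; Inclusion and exclusion criteria). The exclusions are worded as exclusions from the service: they rule out anyone made an inpatient, or already under active case management, when they attend. The criteria section repeats this ("They will be ineligible to participate if they are admitted to the hospital as an inpatient") and adds cognitive impairment, as judged by the referring clinician.

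**Numbers** (Sample size and statistical power). Local data for 2014/2015 indicated that "approximately 1340 people present to emergency departments with suicide-related presentations annually". The plan is 75 participants and 1265 controls.

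**Analysis** (Data analysis; Limitations). Re-presentation and death are compared by Kaplan-Meier curves and a log-rank test, with no adjustment described. The negative binomial model for re-presentation rates adjusts for characteristics such as facility, age, sex and indigenous status. The limitations discuss self-selection and motivation, not unequal eligibility.

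**The concern.** The criteria section has two parts: who is considered (age and significant suicidality) and who is then ruled out (admission, case management, cognitive impairment). The control rule refers only to the inclusion criteria. Read literally, that adds nothing beyond age and a suicidal presentation. Someone who is admitted or already case managed will not be referred, and so meets the no-referral condition for controls.

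The two arms could then differ in eligibility as well as in exposure. Staff decide on admission after assessing suicide risk (Study procedure), so it is plausible, though not shown, that admitted people have a different underlying risk. All three primary hypotheses rest on this contrast. Neither the log-rank tests nor the covariates named as examples would remove such a difference.

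**Working it through.** **1. Criteria side by side**

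| Criterion | Participants | Controls |
|---|---|---|
| Age 16 or over | required | required |
| Suicide-related attendance | required, by clinical assessment | required, by hospital code |
| Not admitted | required | not stated |
| Not actively case managed | required | not stated |
| No precluding cognitive impairment | required, judged by referring clinician | not stated; a non-referred control has no referring clinician |

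**2. The plan's own numbers**

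Inputs from the sample size section: rates p1 = 0.087 and p2 = 0.219, alpha 0.05, power 80%, allocation k = 1265/75 = 16.87. I assume a two-sided test; the protocol does not say.

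- Pooled rate: (0.087 + 16.87 × 0.219)/17.87 = 0.2116.
- n = [1.96 √(0.2116 × 0.7884 × (1 + 1/k)) + 0.8416 √(0.087 × 0.913 + 0.219 × 0.781/k)]² / 0.132² = 66.4, so 67.
- With continuity correction, n = 75. This reproduces the stated intervention number, although the protocol names a log-rank test.
- Controls: 1340 − 75 = 1265 exactly. The target is the whole annual count less the participants, with nothing deducted for ineligible people.

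**3. Controls left after exclusions, and the power cost**

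The ineligible share e is not in the documents, so a range is assumed. One year's pool is 1340(1 − e) − 75. Enrolment runs about two years (November 2017 to November 2019), giving 2680(1 − e) − 75 if people counted in both years are ignored. Power is for the uncorrected two-proportion test at 0.087 against 0.219, with 75 participants and the one-year pool.

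| e | One-year pool | Two-year pool | Power |
|---|---|---|---|
| 0% | 1265 | 2605 | 85.7% |
| 10% | 1131 | 2337 | 85.4% |
| 20% | 997 | 2069 | 85.1% |
| 30% | 863 | 1801 | 84.6% |
| 50% | 595 | 1265 | 83.1% |

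The target of 1265 stays reachable over two years if at least about half of presenters are eligible.

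**4. Possible bias**

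Assume no true effect, a share f of ineligible controls, and a 12-month risk in them r times that of eligible people. Then the apparent risk ratio is 1/[(1 − f) + f × r], whatever the baseline rate. The last two columns take the protocol's 16% re-attempt figure as a stand-in for the rate in eligible people. The chance of a falsely significant benefit is for 75 against 1265, where the nominal value in that direction is 2.5%.

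| f | r | Apparent risk ratio | Control rate | False benefit |
|---|---|---|---|---|
| 10% | 1.5 | 1/1.05 = 0.95 | 16.8% | 3.5% |
| 20% | 1.5 | 1/1.10 = 0.91 | 17.6% | 4.8% |
| 30% | 2 | 1/1.30 = 0.77 | 20.8% | 14.7% |
| 50% | 2 | 1/1.50 = 0.67 | 24.0% | 33.4% |

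**The case against.** The strongest reply is that the authors meant eligible people throughout, and several places fit that:

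- Controls must be people "who met the study inclusion criteria, and who had the closest emergency department presentation dates to the participants", and this phrase can be read as overall eligibility. The same section speaks of referral inclusion criteria for participants and then sets out age, admission and case management together.
- Ineligibility is not among the listed reasons for non-referral, and a lapse in standard procedure presupposes that a referral was due.
- The Treatment as usual section describes an outreach contact within seven days and a letter to the general practitioner. The Study procedure section ties that package to people who are not admitted.
- The end of the Background describes a target population that is neither admitted nor case managed.

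All of this stands as support for an eligible-only reading. It does not settle the matter. The procedural lapse is given only as an example, the treatment-as-usual text allows that other services may already be in place, and no sentence applies the exclusions to controls. Field-level extraction rules can be left to a fuller document, but the article itself defines the control group, and its definition permits the wider reading.

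Three stronger readings are tempting but unsupported:

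- *Controls are chosen on code and age alone.* They are not: the inclusion-criteria condition follows directly.
- *The match 1265 = 1340 − 75 proves that ineligible people are included.* It shows only how the target was set. Two years of recruitment could supply 1265 eligible controls, and taking every presenter would make the same-month, closest-date selection pointless.
- *Only participants are clinically assessed.* The Study procedure section describes a mental health assessment for suicide-related attenders generally. The remaining asymmetry is that controls need a code and no code requirement is stated for participants; nothing says that participants lack one.

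**Conclusion.** The point holds as a gap in the control definition. The exclusions are stated for the service and never for controls. As written, admitted, case-managed or cognitively impaired people can enter the control arm but not the intervention arm, and the control target comes from an unfiltered count. The planned analyses and the stated limitations do not deal with this.

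A reader might infer that the trial is shown to be biased in favour of the intervention. The documents do not support that. They give no share of admitted or case-managed presenters and no risk for them, so both direction and size are assumptions. If the risk in these people is higher, the null risk ratio runs from about 0.95 (10% at 1.5 times) to 0.67 (50% at twice). The first is minor. The second would give about a one-in-three chance of a falsely significant benefit, taking 16% as the rate in eligible people. If the eligible-only reading is what the extraction applies, the bias from admission and case management does not arise; the cognitive exclusion would still be unmatched.

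**What to change.** - State in Study sample that controls must meet the inclusion criteria and, at the index visit, must not have been admitted as inpatients or under active case management by the local health district.
- Name the fields used. Data handling already lists hospital admissions and community mental health data for extraction, so no new source is needed.
- State as a limitation that the cognitive exclusion rests on a referring clinician's judgement and cannot be applied to non-referred controls.
- Restate the number of controls available after these exclusions.
- Keep every enrolled participant in the primary analysis, in line with the stated intention-to-treat approach. Participants without the index code may be left out in a sensitivity analysis only.

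The cost is two filters and a smaller control pool. Because the 75 participants limit precision, power falls only from 85.7% with 1265 controls to 83.1% with 595, the one-year pool if half of presenters were ineligible.

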**Methods:**

A controlled non-randomised two group (intervention vs treatment-as-usual control) design, using an intention-to-treat model, will evaluate the effectiveness of a suicide prevention aftercare intervention providing follow-up after presentations to a hospital emergency department as a result of a suicide attempt or high risk for suicide. The intervention is a community-based service, utilising two meetings with a mental health clinician and follow-up contacts by peer workers via a combination of face-to-face and telephone for four weeks, with the option of extension to 12 weeks. Seventy-five participants of the intervention service will be recruited to the study and compared to 1265 treatment-as-usual controls. The primary hypotheses are that over 12 months, those who participate in the aftercare follow-up intervention are less likely than controls to present to a hospital emergency department for a repeat suicide attempt or because of high risk for suicide, will have fewer re-presentations during this period and will have lower all-cause mortality. As a secondary aim, the impact of the intervention on suicide risk factors for those who participate in the service will be evaluated using pre- and post-intervention repeated measures of depression, anxiety, stress, hopelessness, belongingness, burdensomeness, and psychological distress. Enrolments into the study commenced on 1 November 2017 and are anticipated to cease in November 2019.

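### Control selection and the log-rank tests for hypotheses 1 and 3 ignore index hospital, although participants could not come from all three hospitals until 5 March 2018; the likely bias is small and cheap to reduce

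*Protocol article*

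**What the plan says.** Study duration gives the roll-out. The service "commenced receiving referrals on 21 August 2017 from the emergency department of the largest hospital in the region, the Wollongong Hospital", and "recruitment of study participants commenced on 1 November 2017". It then says "The service was rolled out gradually", with full implementation, "including referrals from all three participating emergency departments, occurred on 5 March 2018". The start dates of the second and third hospitals are not given. The abstract adds: "Enrolments into the study commenced on 1 November 2017 and are anticipated to cease in November 2019".

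Study sample gives the control rule. Controls are people who "either do not receive, or do not accept, a referral to the Aftercare intervention". They are found by "identifying those patients who presented to any of the emergency departments in the study during the study period" and then narrowed to those in the same month, meeting the inclusion criteria, "who had the closest emergency department presentation dates to the participants undertaking the Aftercare intervention". Hospital is not a selection factor, and nothing ties a hospital's controls to the date on which it began referring.

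Data analysis names facility as an example covariate in the negative binomial model for re-presentation rates (hypothesis 2). Repeat presentation and all-cause death (hypotheses 1 and 3) are compared by Kaplan-Meier curves and a log-rank test of the two groups, with no stratification or adjustment mentioned. The Limitations section discusses self-selection but not hospital or the staged start.

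**The concern.** Until a hospital began referring, its patients could become controls but not participants. The participant arm in that period comes only from hospitals already referring, while the control arm can come from all three. Matching on month and date handles season and secular trend; it does nothing for hospital. After the window the rule still does not tie controls to the participant's hospital.

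If 12-month risk differs by hospital, part of any difference between the curves would reflect where people presented and not what Aftercare did. There is some reason in the article to think hospital may matter. The authors adjust for facility in the rate model. Outcomes are also counted only at the three study departments, while Study setting says that the region has several smaller hospitals as well, so capture of a re-presentation may depend on where a person lives. The log-rank test is the one on which the sample size is said to rest, and it is the one left without facility.

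**Working it through.** **Plan's own figure.** The article gives no figure for hospital mix. Its sample size enters here only as the arm sizes, 75 and 1265. The 75 is reproduced by a two-proportion formula with continuity correction (.087 vs .219, two-sided alpha .05, power 80%, ratio 1265/75 = 16.9). Nothing below depends on that calculation.

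**Length of the window.** 1 November 2017 to 5 March 2018 is 124 days. Enrolment to 1 November 2019 is 730 days, and to 30 November 2019 it is 759 days. 124/730 = 17.0%; 124/759 = 16.3%. This is an upper bound for any hospital that joined before 5 March.

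**Controls affected.** Let w be the share of presentations at hospitals not yet referring (assumed 30-50%; not in the article). Controls are chosen by closeness to enrolled participants, so they accrue as participants do. In the window participants can come only from the remaining share, 1 - w. The share of accrual falling in the window is therefore 124(1 - w) / [124(1 - w) + 606], where 606 = 730 - 124.

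- w = 0.3: 86.8 / 692.8 = 12.5%; 0.125 × 1265 ≈ 158 controls; × 0.3 ≈ 48.
- w = 0.5: 62 / 668 = 9.3%; 0.093 × 1265 ≈ 117 controls; × 0.5 ≈ 59.

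That is 48-59 controls, about 4-5% of 1265.

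**Bias under no treatment effect.** Assume a 12-month risk of 16% at the first hospital (the re-attempt figure in Sample size and statistical power, borrowed for this purpose), a risk r times that elsewhere with r from 0.7 to 1.5, all window participants from the first hospital, and the same hospital mix in both arms afterwards. With f the window's share of participants:

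- control risk pc = (1 - w) × 0.16 + w × 0.16r
- participant risk pt = f × 0.16 + (1 - f) × pc
- null hazard ratio = ln(1 - pt) / ln(1 - pc)

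| f | w | r | pt | pc | Null HR | Two-sided type I error |
|---|---|---|---|---|---|---|
| 0.17 | 0.5 | 1.5 | 0.193 | 0.200 | 0.96 | 5.2% |
| 0.17 | 0.6 | 1.5 | 0.200 | 0.208 | 0.96 | 5.3% |
| 0.17 | 0.6 | 0.7 | 0.136 | 0.131 | 1.04 | 5.2% |
| 0.125 | 0.3 | 1.5 | 0.181 | 0.184 | 0.98 | 5.0% |
| 0.093 | 0.5 | 0.7 | 0.138 | 0.136 | 1.02 | 5.0% |
| 0.30 | 0.6 | 1.5 | 0.194 | 0.208 | 0.92 | 6.1% |
| 0.30 | 0.6 | 0.7 | 0.140 | 0.131 | 1.07 | 5.5% |

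With even accrual (f = 0.16-0.17) and w from 0.3 to 0.6, the null hazard ratio lies between about 0.96 and 1.04. With the accrual-consistent shares it is nearer 1, about 0.98-1.02. The f = 0.30 rows show a case in which enrolment was concentrated early.

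**Cost of losing controls.** The precision term is 1/75 + 1/1265 = 0.01412. Without 59 controls it rises by 0.3%, and without 215 (17% of 1265, every control in the window under even accrual) by 1.1%.

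**The case against.** **Confounding is not shown.** A reader might infer that arm is confounded with hospital as a matter of fact. That also needs risk to differ by hospital, and the article gives no risk by hospital. It points to some uniformity: pre-determined codes define the events, and one local health district outreach team makes the follow-up contact. This stands; the point is an exposure to bias, of unknown direction.

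**The control definition may already exclude these patients.** The reasons given for non-participation (declining, lack of time, procedures not followed) seem to presuppose that referral was on offer. But they are given as examples, and the selection sentence covers every study department for the whole study period. The narrower reading is not secured by the text.

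**The count can be inflated.** Even accrual would put about 215 controls in the window and 64-107 of them (30-50%) at hospitals not yet referring. That contradicts its own premise, since participants accrue more slowly while some hospitals cannot refer. The figure of 48-59 is the consistent one.

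**It is partly handled, and the rest could be left to an analysis plan.** The first half is right: hypothesis 2 has facility in its model, so the point does not extend to it. The log-rank test omits age and sex too, so hospital is one instance of a wider gap. But the article states both the selection rule and the test, so this concerns a stated method and not an omitted detail.

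**Excluding controls from hospitals not yet referring could do harm.** A reader might infer that they should be barred. They neither declined nor were passed over, so they are the controls least affected by the self-selection that Limitations names as the main weakness. This objection stands and shapes the fix.

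**Conclusion.** The point holds in a limited form. Control selection ignores index hospital, participants could not come from all three hospitals for up to 124 days, and the comparisons for hypotheses 1 and 3, unlike the rate model for hypothesis 2, do not account for facility.

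The window alone probably does little: 48-59 controls and a null hazard ratio of about 0.96-1.04, or 0.92-1.07 if 30% of participants enrolled in it. Against the planning contrast of .087 vs .219, a hazard ratio of ln(0.913)/ln(0.781) = 0.37, this is minor. These figures rest on an assumed split of presentations, assumed relative risks, and full hospital balance after 5 March 2018. The selection rule does not guarantee that balance. Any later imbalance would come on top, by an amount that cannot be computed from the article. The case for change is that it costs almost nothing, not that the primary result is shown to be unsound.

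**What to change.** 1. In Data analysis, stratify the log-rank comparisons for hypotheses 1 and 3 by index hospital, or use a Cox model with facility as a covariate, in line with the rate model. This loses no controls, and facility is already a planned covariate.
2. In Study sample, add index hospital to month and nearest date as a selection factor where numbers allow.
3. Keep controls from hospitals not yet referring in the main analysis, and repeat it without them as a sensitivity analysis. State each hospital's referral start date so that this can be done.

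The cost is a little more analysis work. If hospital is used in selection, the smaller hospitals may not supply about 17 controls per participant, so some controls may be lost or be less closely dated. Precision is driven by the 75 participants: losing even 215 controls would raise the variance term by only about 1%.
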